### Statistical analysis

Multiple factors that affect this trial will be taken into consideration. Participates from different areas with similar school level will be stratified. A stratified randomizing method will also be adopted according to region, age, gender, etc. Similar stratified groups will be compared; the experimental and the control groups are launched within the same school.

We will use a linear mixed model to analyze incorporating repeated measures. Firstly, visual acuity is independent among subjects and is the primary indicator of observation. Otherwise, it will be measured at the end of each training session and followed up for 3 months. That is important to model the correlation of these repeated measurements.

Statistical analysis using SPSS 20.0 will be performed, and data management software will be used to construct the database. Dedicated staff will be assigned to oversee the management of electronic data, and a clinical research team will be deployed for data entry, validation, reporting, and answering questions. Normally distributed variables will be expressed as their mean and standard deviation (SD), and frequency (percentage) for categorical variables. Baseline characteristics between the intervention and control groups will be compared by performing a two-sample *t*-test and Wilcoxon rank-sum test for continuous variables with and without normal distribution, respectively. All *P*-values are 2-sided and considered statistically significant when less than 0.05.

Primary and secondary observation indexes will be analyzed by the superiority test depending on the treatment, using Per Protocol Set (PPS) and Full Analysis Set (FAS) datasets. The indices of safety evaluation will be analyzed using the Save Set (SS) dataset.

According to the ophthalmic disease efficacy evaluation standard in the Guidelines for Clinical Research of Traditional Chinese Medicine New Drugs:
Cure: visual acuity to normal (5.0)Significant effect: visual acuity improved by 4 lines or more with a visual chartImprovement: visual acuity improved by 2 lines or moreIneffective: visual acuity improved by less than 2 rows or decrease

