**Methods:**

This is a prospective, randomized, multicenter clinical trial. One thousand one hundred forty primary and secondary school students aged 8–18 years old from 27 schools will be recruited and randomly divided into an experimental and a control group at a ratio of 2:1 in two phases, with a training period of 30 days in each phase and a follow-up period of 3 months. No interventions will be conducted during the follow-up period, nor will other interventions employed. Inclusion criteria will meet the diagnostic criteria for simple myopia and −6.00D ≤ spherical lenses ≤ −0.50D and cylindrical lenses ≤1.50D. The primary observation index will be to compare the statistical differences in distant visual acuity between the two groups; the secondary observation indexes will be ocular symptoms (mainly including eye fatigue, dryness, pain, double vision, neck pain, thought disorders, and lags in response), diopter, and astigmatism.

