## Randomization

The random sequence will be designed and processed by the research team of Beijing University of Chinese Medicine. SPSS 20.0 (SPSS Inc., Chicago, IL, USA) software will be used to generate serial numbers for the subjects. Multiple factors that affect this trial will be taken into consideration. Participants from different areas with similar school level will be stratified. A stratified randomizing method will also be adopted according to region, age, gender, etc. Similar stratified groups will be compared; the experimental and the control groups are launched within the same school.

As this study will cover 27 schools, a multicenter trial, stratified randomization will be adopted. Firstly, 27 schools will be allotted east, west, north, south, and middle regions of China. Secondly, schools in each district will be divided into 3 layers according to age. Children aged 8–11 years, 12–14 years, and 15–18 years, severally. This method will minimize errors and improve accuracy.

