### Basic information collection

Information will be collected from the subjects before the start and after the trial is completed, and the main information is as follows.
Basic information: age, nation, grade, height, weight, family history of myopia, parents’ high myopia, etc.Myopia: duration of myopia, possible causes of myopia, naked eye visual acuity, corrected visual acuity, diopter of both eyes, astigmatism, and so onTime allocation for daily activities: including close-range activities (< 50 cm): such as drawing, homework, reading, and using electronic screen terminals such as mobile phones; outdoor activities: including playing outdoors, cycling, hiking, etc.

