### Primary observation indexes

Visual acuity training aims to improve naked eye visual acuity, which affects life and work and will be used as the main observation index. Visual acuity tests were performed before and after each training session for the first 7 days, once a week after 7 days of training and at the first, second, and third months of follow-up, respectively.

The specification for visual acuity testing is based on the “Expert Consensus on Workflow of Myopia Screening in Children and Adolescents (2019)” [21]. The international standard logarithmic visual acuity chart is adopted. During the measurement, the subjects stand 5 m away from the visual acuity chart and cover the contralateral eyes without squinting and oppression. The covered eyes are examined first in the right eye and then in the left eye. If the inspector can identify half or more of the visual markers, check them line by line from top to bottom and ask the subjects to say or gesture the direction of the gap of the visual markers within 5 s. The last line of the visual markers that is correct will be the testee’s vision of that eye. For example, if row 4.8 cannot be identified, check upward until half or more of the rows can be identified.

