## Statistical analysis

### Sample size

The sample size will be estimated based on our early observations [23]. The treatment group was 4.98 ± 0.14, and the control group was 4.92 ± 0.24. Under 20% dropout rate, with the two-tailed *α* = 0.05 and *β* = 0.1 (test efficacy of 0.9), experimental group: control group = 2:1, PASS 15.0 software calculation shows 380 in the experimental group and 190 in the control group. Due to the possible center effect, the final sample size is suggested to be twice expanded. Thus, it is finally confirmed there will be 1140 cases in total, with 760 cases in the experimental group and 380 cases in the control group.

Statisticians suggest that we appropriately expand the sample size to reduce the impact of the central effect on the final results.

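### The primary mixed model states no adjustment for the naked-eye acuity recorded before training; adding it would sharpen the arm comparison at no cost

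*Protocol article*

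**What the plan says.** All references are to the protocol article.

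- **Outcome.** The Primary observation indexes section states: "Visual acuity training aims to improve naked eye visual acuity, which affects life and work and will be used as the main observation index". The abstract's Methods states the comparison as "compare the statistical differences in distant visual acuity between the two groups". Change from baseline is not mentioned there.
- **Model.** Statistical analysis: "We will use a linear mixed model to analyze incorporating repeated measures". The reason given is that acuity is read repeatedly: "it will be measured at the end of each training session and followed up for 3 months". No fixed effects or covariates are listed.
- **Baseline readings.** Basic information collection, done before the start and after the end of the trial, includes "naked eye visual acuity, corrected visual acuity, diopter of both eyes, astigmatism". Table 1 marks current visual acuity at enrollment (-7~0 d) and at allocation (0 d). Primary observation indexes adds: "Visual acuity tests were performed before and after each training session for the first 7 days".
- **Stated uses of baseline.** Baseline characteristics are compared between arms by t-test or rank-sum test. The efficacy categories count lines gained on the chart, which also needs a starting value.
- **Sample size.** "The treatment group was 4.98 ± 0.14, and the control group was 4.92 ± 0.24". These are acuity levels.
- **Stratification.** Randomization: "A stratified randomizing method will also be adopted according to region, age, gender, etc". Baseline acuity is not named among the factors.

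**The concern.** Entry covers refractions from -0.50 D to -6.00 D, so unaided acuity can be expected to differ widely between children before any training. In a comparison of post-training levels, that spread adds noise. The planned difference is only 0.06 on the chart scale. The named strata do not balance acuity, and a significance test on baseline values does not change the effect estimate.

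At stake is the precision of the phase 1 arm difference, on which the decision about phase 2 depends. The value that would remove part of the noise is already being collected.

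**Working it through.** **Inputs from the Sample size section:** difference d = 4.98 − 4.92 = 0.06; SDs 0.14 (experimental) and 0.24 (control); two-sided α = 0.05; power 0.90; ratio 2:1; dropout 20%; 760 + 380 children. Evaluable children: 760 × 0.8 = 608 and 380 × 0.8 = 304.

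**Assumed, because the documents do not give them:** baseline-to-outcome correlation ρ of 0.3, 0.5 or 0.7, equal in both arms; baseline SDs equal to the outcome SDs; design effect DE of 1 to 2.

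**1. The plan's own figure.** Control n = (1.960 + 1.282)² × (0.24² + 0.14²/2) / 0.06² = 10.507 × 0.0674 / 0.0036 = 196.7. This gives 197 control and 394 experimental children before dropout, and 247 + 494 after dividing by 0.8. The stated 380 + 190 is therefore not reproduced at 90% power with 20% dropout. That is a separate matter; the steps below use the final 760 + 380.

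**2. Unadjusted precision, no centre effect.** SE = √(0.14²/608 + 0.24²/304) = √(0.0000322 + 0.0001895) = 0.0149. The 95% CI half-width is 1.96 × 0.0149 = 0.029. Power = Φ(0.06/0.0149 − 1.96) = 98.1%.

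**3. With baseline adjustment.** The variance is multiplied by about (1 − ρ²), so SE and CI width are multiplied by √(1 − ρ²). This is a single-reading approximation to the repeated-measures model.

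| ρ | 1 − ρ² | SE | CI half-width | CI narrower by | Power, DE = 1 | Power, DE = 1.5 | Power, DE = 2 |
|---|---|---|---|---|---|---|---|
| none | 1 | 0.0149 | 0.029 | – | 98.1% | 90.8% | 81.3% |
| 0.3 | 0.91 | 0.0142 | 0.028 | 5% | 98.8% | 93.2% | 84.8% |
| 0.5 | 0.75 | 0.0129 | 0.025 | 13% | 99.6% | 96.7% | 90.8% |
| 0.7 | 0.51 | 0.0106 | 0.021 | 29% | 99.99% | 99.6% | 97.9% |

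SE and half-width are shown for DE = 1; multiply them by √DE otherwise. The power columns for DE above 1 also assume that adjustment shrinks the centre-level variance in the same proportion as the between-child variance.

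**4. Chance imbalance.** At 760 + 380, a baseline difference of 1.96 SE is 1.96 × √(0.14²/760 + 0.24²/380) = 0.026. With equal SDs the baseline-outcome slope is ρ, so an unadjusted level comparison carries ρ × 0.026:

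- ρ = 0.3: 0.008, or 13% of the 0.06 target
- ρ = 0.5: 0.013, or 22%
- ρ = 0.7: 0.018, or 30%

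**The case against.** The strongest reply is that silence is not a decision. The Statistical analysis section lists no model terms at all, not even arm or visit, and a covariate list is commonly left to the analysis plan, which is not shown. The sentence about readings explains why correlation must be modelled and need not define the response set. Pre-session readings are scheduled, and the Missing data section bases the primary analysis on all observed data. All of this stands. A reader might infer that the plan has chosen an unadjusted analysis or ruled baseline out. The text does not support that. A reader might also infer that baseline values serve only for significance tests, but the line-gain categories use them too.

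The second reply concerns size. The gain from 81% to 91% needs a design effect of 2. The only source for that is the doubling of the sample as a precaution against a possible centre effect. Both arms run within the same school, so shared school differences largely cancel in the arm contrast. Quality control does put the arms in separate classrooms with different teachers, so some clustering by training group is conceivable. The documents give no figure for it, and baseline adjustment would not necessarily remove variance of that kind. This reply also stands.

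Third, chance imbalance under randomisation is random error that the confidence interval already covers. It carries over only in proportion to the baseline-outcome slope.

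What survives is narrower. The comparison, the sample size and the readings named beside the model all concern levels after training, and no stated step uses the recorded baseline to improve the effect estimate.

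**Conclusion.** The point holds as a free improvement, not as an error that invalidates the trial. If the model is run as described, the arm comparison remains valid, with a wider interval than necessary and chance imbalance left uncorrected. The interval would be about 5%, 13% or 29% narrower at assumed correlations of 0.3, 0.5 or 0.7.

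A reader might conclude that the trial is underpowered without adjustment, or that its estimate would be biased. Neither is supported. Power is already about 98% at 608 + 304 with no centre effect, where adjustment adds at most about 2 points. The larger power gain depends on a design effect that the documents do not give and that allocation within schools makes doubtful.

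**What to change.** In the Statistical analysis section, specify the primary linear mixed model as follows:

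- Day-0 pre-training naked-eye acuity enters as a fixed covariate, or as the first response with a common mean across arms.
- Arm, visit and arm-by-visit are fixed effects.
- The randomisation factors region, age layer and gender are fixed effects.
- The baseline-adjusted arm difference is the primary phase 1 result.
- Diopter, astigmatism and CISS, which Table 1 also schedules before training, use the same baseline-adjusted form.

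The cost is analysis wording only. It needs no extra visits, measurements or children, and the few added degrees of freedom are negligible at this sample size.

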#### First training

The first set of audio and video training exercises will be projected in the classroom by the vision acuity training tutor, and the students will be guided by the audio-visual movements and verbal commands to perform the following exercises.
Abdominal breathing: Inhale through the nose, exhale through the mouth, bulge abdomen while inhaling, tighten abdomen while exhaling; start doing abdominal breathing when hearing the words of “adjust your breath and inhale.”Eye-warning exercise: Rub your hands more than 30 times, cover your eyes with the palms, place thumbs on the temples, clasp four fingers on your forehead, and leverage the temperature of your palms to warm eyes; after the temperature gradually dissipates, use Yuji acupoints of the palms to gently press your eyes 5 times, with moderate intensity; start eye-warning exercise when you hear the words “get ready to press” and “quickly rub your hands” during training.Healthy vision exercise: Press both hand palms on your ears, place fingers on the back of your head; do not move the palms, and use fingers to gently tap the back of your head. During the training, when you hear “healthy vision exercise,” start doing it.Activate Shixuan acupuncture point: Tap your fingers on your palm, shake your palm, and make an arrow shape.Play the “1-Audio,” turn off the lights in the classroom, close the curtains, and try to create a dark environment. Remain quiet the entire time. Close your eyes until the audio says to open them. Follow the audio to imagine and do movements, e.g., “Use the fingertips of one hand to gently touch the center of the palm of the other, and then shake your hand vigorously.”Play the “C-video,” a video about lotus flowers to stimulate the imagination and match the 2-Audio with the images that appear in the video. For example, “On a calm lake, you can definitely see the vivid color of the lotus flowers and the greenish-blue leaves of the lotus .......”Demonstration and correction. Make a hollow bowl shape with your hands (thumbs on the second knuckle of your index finger) and clasp them over your eyes, with palms facing your eyes.Play “2-Audio” and do the eye stretches: Close your eyes and move them from front to back as if a train is moving back and forth in a tunnel.Play “3-Audio” and listen to the audio with your hands in a hollow bowl shape over your eyes the whole time. When the audio says “in,” put pressure on your eyes for 1 s, and when it says “out,” relax your eyes and perform the related imagery and actions. When the audio says “pull” in future exercises, let your eyes enter a state just like going into a tunnel, hold for 1 s, and then relax.Play “D-Video (Ball of Light)” to stimulate imagination and introduce natural light.Play “4-Audio” to build up the confidence of myopia sufferers to restore their eyesight.The above training will be repeated on the 8th day to intensify the effect, for 1 h.

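### The protocol gives two schedules for reading the primary visual acuity, and nothing keeps post-session readings out of the mixed model, so a net transient session effect can enter the efficacy estimate

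*Protocol article*

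**What the plan says.** The Abstract defines the primary outcome without a time point: "The primary observation index will be to compare the statistical differences in distant visual acuity between the two groups". Two later sections say when acuity is read, and they differ.

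- Primary observation indexes: "Visual acuity tests were performed before and after each training session for the first 7 days, once a week after 7 days of training", and then "at the first, second, and third months of follow-up". The weekly tests have no stated timing relative to that day's session.
- Statistical analysis: "it will be measured at the end of each training session and followed up for 3 months". This sentence supports the use of a linear mixed model for the repeated readings.

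Table 1 marks acuity in every phase 1 training column and does not place it before or after the session. The Missing data section bases the primary analysis on all observed data. No section sets any class of reading aside.

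The sessions differ by arm. In the experimental arm, the First training section has the subject "use Yuji acupoints of the palms to gently press your eyes 5 times" as part of the eye-warming exercise. A later audio cue is to "put pressure on your eyes for 1 s". The Daily vision acuity training section repeats the eye-warming movements and adds 10 minutes of reading character cards at the distance where they begin to blur. The control arm massages acupoints around the eyes, with taught intensity and direction, for 15–20 minutes on 28 of the 30 days. No palm pressing on the eyes and no distance-reading drill is described for it.

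**The concern.** The outcome section says that the aim is unaided acuity as it affects life and work. A change that fades soon after a session does not answer that. If readings taken just after a session feed the efficacy contrast, any short-lived difference between the two kinds of session is counted as a treatment effect. The card drill resembles the chart test that follows it, so a practice or warm-up effect is plausible. Pressing on the eyes could act in either direction.

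The same readings can reach other decisions: the phase 1 comparison on which phase 2 depends, the response categories, the last result taken as final for withdrawn subjects, and the clause on early discontinuation after cure. Timing is protocol content. An analysis plan can choose among readings, but it cannot recover a pre-session reading that was never taken.

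**Working it through.** **The plan's own figure.** The plan gives no figure for a session effect. Its related figure is the sample size: difference 4.98 − 4.92 = 0.06, SDs 0.14 and 0.24, two-sided 0.05, power 0.9, 2:1, 20% dropout, stated as 380 + 190. With unequal SDs, n(control) = (1.960 + 1.282)² × (0.24² + 0.14²/2) / 0.06² = 197, and 197/0.8 gives 247 after dropout. The stated 190 is not reproduced this way. That is a separate matter. Only the 0.06, the SDs and the final 760 + 380 are used below.

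**Share of post-baseline readings that follow a session** (equal weights assumed; the day 1 pre-session test is baseline and is left out):

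- Outcome section: 6 pre-session (days 2–7) + 7 post-session (days 1–7) + about 3 weekly + 3 follow-up = 19. Post-session share 7/19 = 37%.
- The same, if the weekly tests also follow a session: 10/19 = 53%.
- Analysis section as worded: 30 sessions + 3 follow-up = 33. Share 30/33 = 91%.

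**Spurious difference** = net transient effect × share, with no lasting effect. The documents give no size, so 0.01, 0.03 and 0.06 are assumed (0.1, 0.3 and 0.6 of a 0.1-unit chart line).

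| Net transient effect | 7/19 | 10/19 | 30/33 |
|---|---|---|---|
| 0.01 | 0.004 | 0.005 | 0.009 |
| 0.03 | 0.011 | 0.016 | 0.027 |
| 0.06 | 0.022 | 0.032 | 0.055 |

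As a share of the planned 0.06, the 7/19 column is 6%, 18% and 37%, and the 30/33 column is 15%, 45% and 91%.

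**Yardstick.** After 20% dropout, 760 × 0.8 = 608 and 380 × 0.8 = 304. SE = √(0.14²/608 + 0.24²/304) = 0.0149, so a difference of about 1.96 × 0.0149 = 0.029 is significant. The chance of a significant result with no lasting effect (Welch test, nominal 5%) is:

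| Net transient effect | 7/19 | 10/19 | 30/33 |
|---|---|---|---|
| 0.01 | 5.7% | 6.4% | 9.3% |
| 0.03 | 11.5% | 18.5% | 44.7% |
| 0.06 | 31.6% | 56.2% | 95.5% |

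These figures treat the average of the readings as one reading with the planning SDs and ignore clustering by school.

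**After the change.** If no post-session reading enters the contrast, the share is 0, the contribution is 0 and the false-positive rate returns to 5%. Power for 0.06 at 608 + 304 is 98.0%, ignoring centre effects.

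**The case against.** The strongest defence is that the outcome section is the real specification, and that the analysis section's clause is loose wording meant to justify modelling correlation. On that view the design already holds paired readings before and after sessions, which isolate an acute effect, and follow-up readings in months when no training is given, which test persistence. An unseen analysis plan may also define the contrast. Part of this stands: the 91% share arises only from the analysis section's wording. But the article does not say which schedule governs, leaves the weekly tests untimed and excludes no reading.

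A reader might go further in three ways that the documents do not support.

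- *That primary acuity is read only after sessions.* The outcome section has "Visual acuity tests were performed before and after each training session for the first 7 days", and the follow-up readings are training-free.
- *That only the experimental arm can show a session effect, and that it must favour that arm.* Controls massage around the eyes, so any bias is the net of two session effects. No document reports the size or sign of either. The pressure cue is also ambiguous, because the hands are then held in a hollow bowl shape over the eyes. The darkened room is described only for the long sessions of days 1 and 8.
- *That the protocol breaks its own ban on eye pressure.* The instruction to "cover the contralateral eyes without squinting and oppression" governs how the other eye is covered during the test. It does not cover what happens beforehand.

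On the arithmetic, equal weighting is an assumption. Under the outcome section's 7/19, even the top of the assumed range (0.022) stays below the 0.029 threshold.

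**Conclusion.** The point holds as a conflict between two sections together with a route for bias. The sections disagree on when the primary outcome is read, and nothing keeps post-session readings out of the model. A net transient effect can therefore enter the estimate; the documents do not show that it will. Under the assumed 0.01–0.06 it would amount to about 0.004–0.022 on the outcome section's schedule, or 0.009–0.055 on the analysis section's wording, against a planned 0.06. These sizes rest on equal weights, about three weekly readings, no lasting effect and no clustering. A bias in either direction would distort the answer, and avoiding it is cheap, so the change should be made.

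**What to change.** 1. Reconcile the Primary observation indexes and Statistical analysis sections. In the latter, state that training-period acuity is read before that day's session.
2. Time the weekly tests after day 7 before the session.
3. Base the primary contrast and the response categories on off-session readings: pre-session and months 1–3.
4. Keep the post-session readings of days 1–7 and report them separately as a description of the acute effect.
5. For the early-discontinuation clause on cure in the Suspension criteria, reconcile that section with the two above on which reading applies.

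The cost is protocol wording and a shift in when the weekly tests are done. The pre-session readings of days 1–7 are already planned. On the outcome section's count, 6 + 3 + 3 = 12 of 19 post-baseline readings remain. The drawbacks are fewer readings in the primary contrast and possibly a smaller observed effect.
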